**Figure 1 F1:**
[figure not shown]
Flow chart of the MASTER trial. V1 screening includes prescreening of patients for inclusion criteria and inclusion for additional screening of exclusion criteria. Randomisation occurs within 7 days of stroke onset. V2 includes randomisation and initial assessments (imaging and clinical), carried out within 24 hours of beginning of intervention medication. V3 and V4 include one clinical assessment. V5 is the primary outcome time point, including both imaging and clinical assessments. V6 represents the 180 days follow-up. Telephone check-ins occur between each in-person visit. MASTER, Maraviroc for Stroke Recovery; mRS, modified Rankin Scale; NIHSS, National Institutes of Health Stroke Scale; FLAIR, Fluid-Attenuated Inversion Recovery; DWI, Diffusion-Weighted Imaging; MRSI, Magnetic Resonance Spectroscopic Imaging.

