### Statistical methods for primary and secondary outcomes

Two analysis sets will be used: an intention-to-treat population (all randomised participants who received ≥1 dose, analysed per allocation) and a per-protocol population (excluding those with major protocol deviations, eg, <80% medication adherence). Missing data will not be imputed.

The primary outcome (FMA-UE) will be compared between groups using a t-test or non-parametric equivalent. An adjusted analysis using multivariate linear regression will account for stratification variables (infarct side, finger extension ability) as well as other variables like CCR5-Δ32 loss-of-function mutation carrier status to account for confounding effects on motor recovery and treatment response. Secondary outcomes will be analysed via regression models adjusted for the same covariates. Linear mixed models will include time point and group as fixed effects and participant ID as a random effect to account for repeated measures. To assess whether maraviroc promotes recovery via peri-infarct plasticity, causal mediation analysis will estimate direct and indirect effects (via changes in connectivity/metabolism from baseline to 90 days). The analysis includes three regression steps, with the indirect effect tested via the Sobel method. Weekly rehabilitation hours (during the first 90 days) will be included as a covariate. A similar approach will be applied to motor learning outcomes. Safety analyses will summarise the number and proportion of participants with ≥1 SAE, AE of special interest, or death by day 90 in each group.

Analyses will be conducted in R, MATLAB or Python using appropriate packages. Imaging data will be processed with FSL, FreeSurfer, SPM and DSI Studio, depending on modality.

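### The mediation analysis is called causal, but randomisation does not protect its mediator-to-outcome path, and baseline FMA-UE, infarct volume and the baseline MRI value are not named as covariates

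*Protocol article*

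**What the plan says.** All of this is in the protocol article, under Statistical methods for primary and secondary outcomes, unless noted.

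- **Aim:** "To assess whether maraviroc promotes recovery via peri-infarct plasticity, causal mediation analysis will estimate direct and indirect effects". The same sentence goes on to define the mediator: "causal mediation analysis will estimate direct and indirect effects (via changes in connectivity/metabolism from baseline to 90 days").
- **Procedure:** "The analysis includes three regression steps, with the indirect effect tested via the Sobel method".
- **Covariate named alongside it:** "Weekly rehabilitation hours (during the first 90 days) will be included as a covariate". A similar approach is planned for motor learning.
- **Other adjusted models:** the adjusted primary model "will account for stratification variables (infarct side, finger extension ability) as well as other variables like CCR5-Δ32 loss-of-function mutation carrier status", and "Secondary outcomes will be analysed via regression models adjusted for the same covariates". The article does not say whether these covariates also enter the mediation regressions.
- **Baseline data:** the Figure 1 legend says "V2 includes randomisation and initial assessments (imaging and clinical"), and the Primary outcome section has FMA-UE measured at every time point. Baseline FMA-UE and baseline MRI are therefore collected. Neither they nor infarct volume are named as covariates anywhere in the article.

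**The concern.** The indirect effect is the product of path *a* (arm to MRI change) and path *b* (MRI change to day-90 outcome, given arm). Randomisation makes *a* causal. Path *b* is an association among patients, and it is causal only if nothing left out of the model drives both MRI change and recovery. Initial severity and infarct size are obvious candidates, since eligibility admits any FMA-UE below 63/66 with at least 10° of finger extension.

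The null that the Sobel test actually addresses is that *a* is zero or that mediator and outcome are unassociated given the covariates. The stated question is whether drug benefit passes through plasticity. If maraviroc moves an MRI marker that plays no part in recovery, confounding of *b* can still yield a significant indirect effect. Changing the standard error, for example to a bootstrap, would not remove this.

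What is at stake is the mechanistic conclusion. The Introduction names mechanisms of action as an aim, and the Abstract lists peri-infarct plasticity among the secondary outcomes.

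**Working it through.** **1. Sample size.** Inputs from Sample size estimate: difference 12.4, SD 17.5, 5% type I error (two-sided assumed), 80% power, 20% dropout. Per arm: 2 × (1.96 + 0.8416)² × (17.5/12.4)² = 2 × 7.849 × 1.992 = 31.3, so 32. Total 64, and 64/0.80 = 80. The plan's figure reproduces. Missing data are not imputed, so about 64 to 80 patients would be analysed. No sample-size figure is given for the mediation test.

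**2. Size of the spurious indirect effect.** The documents give no confounding strengths, so these are assumptions. Let U be mildness of the initial stroke, with correlation 0.5 with MRI change and 0.7 with day-90 FMA-UE (within arm, unit SDs). Let rehabilitation hours correlate −0.3 with U, and let the drug shift the mediator by *a* = 0.7 SD. The mediator has no effect on outcome. Adjusting for hours only:

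- variance of U left = 1 − 0.3² = 0.91
- covariance of mediator and outcome = 0.5 × 0.7 × 0.91 = 0.3185
- variance of mediator = 1 − 0.5² × 0.09 = 0.9775
- spurious *b* = 0.3185/0.9775 = 0.326
- spurious indirect effect = 0.7 × 0.326 = 0.228 SD, and × 17.5 = 4.0 FMA-UE points

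Simulation also gives about 4.0 points, or about 2.7 with side and finger extension added. The total effect is unbiased, so the direct effect is biased by the same amount in the opposite direction.

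**3. False-positive rate.** Mediator regressed on arm and covariates; outcome regressed on arm, mediator and covariates; z = ab/√(a²·SE_b² + b²·SE_a²); reject if |z| > 1.96. The true mediator effect is zero, n = 64, with 2,000 to 3,000 runs per setting. Ranges come from separate runs with shifts of 0.7 and 0.71 SD and different strengths for the finger-extension proxy.

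| Drug shift (SD) | Correlation of U with MRI change / FMA-UE | Hours only | + side, finger extension | + baseline severity |
|---|---|---|---|---|
| 0 | 0.5 / 0.7 | <1% | <1% | <1% |
| 0.7 | 0.3 / 0.5 | 6% | 3–4% | 1% |
| 0.7 | 0.5 / 0.5 | 18% | 8–12% | 1–2% |
| 0.7 | 0.5 / 0.7 | 38–39.5% | 19–28% | 2% |
| 1.0 | 0.3 / 0.5 | 11% | 5% | 2% |
| 1.0 | 0.5 / 0.7 | 61–62% | 32–46% | 3–4% |
| 0.7 | −0.4 / 0.7 | 24% | 15% | 1% |

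The spread in the strata column reflects how closely a two-level finger-extension variable tracks severity: the upper ends assume a latent correlation of 0.6, the lower ends about 0.8. With 80 patients and a shift of 0.71, hours only gives 58% at 0.5/0.7 and 9% at 0.3/0.5. A true direct drug effect of 0.71 SD leaves the n = 64 rates at 0.5/0.7 unchanged.

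**4. Direction.** In the last row the spurious indirect effect is negative. Modelling the change score explicitly with regression to the mean (correlation with U about −0.4) gives 27% false negative-direction results with hours only and 12% with the strata.

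**5. How much the fix removes.** If baseline severity is measured with reliability 0.8, the rate after adjustment at 0.5/0.7 is 3.9% (shift 0.7) or 7.4% (shift 1.0). In an explicit change-score model with strong confounding (correlation of MRI change with U 0.61), adjusting for strata, baseline FMA-UE and baseline MRI takes the rate from 57% to 2–6% at n = 64, and from 74% to 3–11% at n = 80.

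**The case against.** The strongest reply is that the article nowhere calls rehabilitation hours the sole mediation covariate. The hours sentence follows shortly after an open-ended covariate list, so hours may be an addition to it. Finger extension, a stratification factor that the article ties to motor severity, would then already be in the model. A final analysis plan is foreseen before unblinding and could complete the list. This stands in part. A reader might infer that the plan ignores baseline severity altogether; the text does not support that, because carry-over is unstated rather than excluded. But the article does fix the mediator, the test, one post-randomisation covariate and the word causal, and the strata column shows that carry-over would not be enough under moderate to strong confounding.

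A second reply is that three regression steps may mean the arm-to-outcome effect must also be significant. With no drug effect on recovery, such a gate brings the shift-0.7, 0.5/0.7 rates down to 2.1% (hours) and 1.4% (strata). The article states no such gate, and with a true direct effect of 0.71 SD the gated rates are still 33% and 23%. The realistic risk is therefore an effective drug whose mechanism is misattributed.

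A third reply is that the large rates need a mediator shift about as large as the effect the trial is powered for (12.4/17.5 = 0.71 SD) and substantial confounding. That is correct and limits the claim.

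Finally, the MRI measures sit under Other outcomes in the body of the article, and the Discussion speaks of exploring mechanisms. That bears on priority, not on whether the estimate is biased.

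**Conclusion.** The point holds in a limited form. As written, the analysis does not support a causal reading of the indirect effect. Confounding of the mediator-to-outcome path by initial severity is addressed at best through a two-level proxy, and perhaps not at all. Under the central assumptions (shift 0.7 SD, correlations 0.5 and 0.7, 64 patients) the false-positive rate is about 39% with hours only, 19–28% with the strata and 2% with baseline severity.

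It would be wrong to infer that the plan will report false mediation. Inflation needs both a real drug effect on the MRI marker and at least moderate confounding. With no drug effect on the mediator there is none, and at correlations of 0.3 and 0.5 with a 0.7 SD shift the rate is about 3–6% at 64 patients. Nor is the bias necessarily in favour of mediation: if MRI change correlates negatively with mildness, a true mediated effect could be masked or reversed. The comparison of FMA-UE between arms and the safety analyses are untouched. The change should be made, but it concerns the mechanistic claim only.

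**What to change.** In both the mediator and the outcome regressions, prespecify adjustment for baseline FMA-UE, the baseline value of the MRI mediator, baseline infarct volume from the V2 MRI and the two stratification factors. In the motor-learning counterpart, use the baseline motor-learning score in place of baseline FMA-UE. State the assumption of no unmeasured mediator-outcome confounding, add a sensitivity analysis for a residual mediator-outcome correlation, and describe the result as consistent with mediation unless the indirect effect survives it.

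The cost is analysis-plan wording and some extra analysis, with no new visits or scans. Because the final analysis plan is to be validated before unblinding, this can be settled while blinded. The downsides are a few more parameters with about 64 evaluable patients, and some residual bias where baseline FMA-UE measures severity imperfectly, which is why the sensitivity analysis is needed as well.

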### Study design

MASTER is a single-centre, patient and investigator-blinded, randomised, placebo-controlled, phase 2 clinical trial. It assigns patients with acute ischaemic stroke (within 7 days of onset) and motor impairment to either maraviroc (2×300 mg/day) or placebo for 90 days. The trial will randomise at a 1:1 ratio, powered to assess the superiority of maraviroc over placebo. The trial will be conducted at the Stroke Centre of the Geneva University Hospital, Switzerland.

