### Intervention

The experimental intervention will be the administration of Maraviroc. The dosage will be 300 mg two times per day orally (2 capsules of 150 mg in the morning and 2 capsules of 150 mg in the evening). The experimental product will be reconditioned by the HUG pharmacy (crushed, mixed with mannitol and prepared in a capsule) from the original product to match the placebo. Placebo will be mannitol in identical capsules.

All patients will be treated with standard of care including secondary stroke prevention strategies in line with institutional and European guidelines (European Stroke Organisation guidelines on secondary stroke prevention^8^). All participants will receive standard neurorehabilitation according to our institutional stroke rehabilitation programme, aligned with European Stroke Organisation guidelines,^9^ which is currently recommended to include a minimum of 20 hours of intensive repetitive arm training 3–5 times per week over 4–6 weeks. During inpatient rehabilitation, detailed information on therapy content and focus (including upper-limb-specific and task-oriented training) will be recorded. During outpatient rehabilitation, rehabilitation exposure will be quantified by weekly therapy hours. This will enable controlling both for the number of hours of therapy received and percentage of patients meeting ESO guideline requirements, based on the reported therapy content.

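### Rehabilitation hours over the first 90 days, a post-randomisation variable, are a covariate in the mediation analysis and can bias the effects estimated there

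*Protocol article*

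**What the plan says.** All references are to the protocol article.

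- *Statistical methods for primary and secondary outcomes*, primary test: "The primary outcome (FMA-UE) will be compared between groups using a t-test or non-parametric equivalent". No covariate enters here.
- Same section, adjusted FMA-UE regression: the stratification variables, "as well as other variables like CCR5-Δ32 loss-of-function mutation carrier status". The list is open-ended and does not name rehabilitation hours. Secondary outcomes use the same covariates.
- Same section, mechanism: "causal mediation analysis will estimate direct and indirect effects (via changes in connectivity/metabolism from baseline to 90 days"), in three regression steps with a Sobel test. The next sentence is "Weekly rehabilitation hours (during the first 90 days) will be included as a covariate". Motor learning is then to be handled in a similar way.
- *Intervention*: for outpatients, "rehabilitation exposure will be quantified by weekly therapy hours". The purpose of recording therapy is also given: "This will enable controlling both for the number of hours of therapy received and percentage of patients meeting ESO guideline requirements".
- *Study design*: patients receive "either maraviroc (2×300 mg/day) or placebo for 90 days".

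**The concern.** The covariate window and the treatment window are the same 90 days, and both end at the primary outcome visit. Hours are observed, not fixed: *Intervention* cites a recommended minimum, and nothing makes hours independent of how well a patient is doing. If maraviroc speeds recovery and recovery changes the therapy a patient receives, hours are partly a consequence of treatment. Holding them constant then removes part of the effect and can open a path through shared causes of hours and outcome.

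At stake is the mechanistic conclusion, that any benefit runs through peri-infarct plasticity. The Introduction names mechanism of action as an aim of the trial. A second risk comes from the general intent stated in *Intervention* together with the open covariate list: hours could also be carried into the adjusted FMA-UE and secondary models.

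**Working it through.** **Scale.** The planning figures are a difference of 12.4 and an SD of 17.5. They reproduce the stated sample size: n per arm = 2 × (1.960 + 0.842)² × (17.5/12.4)² = 31.3, so 32. Then 64/0.80 = 80. Two-sided 5% is assumed. The values 12.4 and 17.5 set the scale below. Every other coefficient is an assumption, because the documents give none.

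**Case 1: hours respond to recovery and do not affect outcome.** A is treatment, M the mediator, E recovery, H hours in SD units, Y the FMA-UE score.
- M = 1·A + noise (variance 1)
- E = 6.4·A + 6·M + noise (variance 8² + 11² = 185)
- H = (h/17.5)·E + noise (variance 1 − h²)
- Y = E + noise (variance 81)

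True effects: direct 6.4, indirect 1 × 6 = 6.0, total 12.4. The within-arm variance of E is 36 + 185 = 221, and the SD of Y is √(221 + 81) = 17.4.

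Total effect with H in the model = 12.4 − β × (h/17.5) × 12.4, where β = (h/17.5)·221 / [(h/17.5)²·221 + 1 − h²].
- h = ±0.5: |β| = 6.314/0.930 = 6.79 and the shift in H is 0.354 in size. Total = 12.4 − 6.79 × 0.354 = 10.0.
- h = ±0.3: |β| = 3.789/0.975 = 3.89 and the shift is 0.213. Total = 12.4 − 3.89 × 0.213 = 11.57 (a simulation of 500,000 patients gave 11.54).

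The sign of h cancels because β and the shift change sign together. The same algebra with 185 in place of 221 gives the direct effect:

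| h | Total | Direct | Indirect |
|---|---|---|---|
| 0 | 12.4 | 6.4 | 6.0 |
| ±0.3 | 11.6 | 6.0 | 5.5 |
| ±0.5 | 10.0 | 5.3 | 4.7 |

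The loss in the total is 0.83/12.4 = 7% at ±0.3 and 2.4/12.4 = 19% at ±0.5. If the drug has no effect, this model gives no bias.

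**Case 2: the drug acts on hours directly.** Let H = −0.3·A + noise, with hours adding 5 points per SD. The true total is 12.4 + 5 × (−0.3) = 10.9. With H in the model the estimate is 12.4, which is too high.

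**Case 3: hours confound mediator and outcome, and the drug does not change them.** Let M = A + 0.5·H + noise (variance 1) and Y = 6.4·A + 6·M + 5·H + noise, with Var(H) = 1. Truth: direct 6.4, indirect 6.0. With H the models recover both. Without H the coefficient of M becomes 6 + 5 × 0.5/1.25 = 8, which gives direct 4.4 and indirect 8.0. If the mediator variance is 2.5 instead of 1.25, the shift is 1.0 and the split is 5.4 and 7.0.

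**Case 4: cases 2 and 3 together.** The effect of A on M is 1 − 0.5 × 0.3 = 0.85. Truth: indirect 0.85 × 6 = 5.1, direct 6.4 − 1.5 = 4.9, total 10.0.
- H in every step: direct 6.4, indirect 1 × 6 = 6.0.
- H in no step: indirect 0.85 × 8 = 6.8, direct 10.0 − 6.8 = 3.2.
- H in the mediator-outcome step only, direct effect taken as total minus indirect: indirect 0.85 × 6 = 5.1, direct 4.9.

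Neither all-in nor all-out is right. The third line works only because the model is linear, has no interaction, and puts hours before the mediator.

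**The case against.** The sentence stands between the Sobel description and the motor-learning sentence, so by placement it governs an explanatory analysis and not the efficacy comparison. The primary test is unadjusted, and the adjusted FMA-UE regression does not name hours. The remark in *Intervention* says why hours are recorded and names no model. This stands. A reader might infer that the covariate could explain away a real effect in the primary result. The documents do not support that.

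It can also be said that no document shows hours responding to recovery, that the coefficients above are assumed, and that the bias need not be a loss. All of this stands: the bias is zero when hours do not respond, and case 2 runs upward.

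The strongest objection is that therapy may drive both plasticity and FMA-UE. Randomisation does not protect the mediator-outcome relation, so adjusting for hours there has a recognised purpose. Case 3 bears this out: dropping hours then inflates the indirect effect. A reader might conclude that hours should simply be removed from the whole mediation analysis. That remedy is wrong for the mediator-outcome step. The objection does not rescue the stated plan, however. Once treatment also changes hours, putting them into all three regressions fails too (case 4).

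**Conclusion.** The point holds as a risk in a specified analysis: conditioning on hours can bias the effects, but it need not. The protocol positively names a post-randomisation covariate for the mediation analysis and its motor-learning counterpart, so this is not a detail left to an unseen analysis plan. If hours respond to recovery with a standardised dependence of ±0.3 to ±0.5, a 12.4-point total effect is estimated at about 11.5 to 10.0, with both components reduced. A direct drug effect on hours can reverse the direction. If hours are also a mediator-outcome confounder, the three regressions and the Sobel test do not identify the direct and indirect effects.

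The sizes rest on assumed linear models. The structural conclusion rests only on hours being measured after randomisation and being open to change by treatment. The primary t-test and the sample size of 80 are untouched. Whether the adjusted FMA-UE and secondary regressions would include hours is unclear from the text and should be settled.

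**What to change.** 1. State that no model estimating the effect of maraviroc includes rehabilitation hours or guideline attainment. This covers the adjusted FMA-UE regression, the secondary regressions, the mixed models, and the total-effect and treatment-to-mediator steps of the mediation. The same applies to motor learning.
2. Use baseline covariates only in those models and close the list. Include baseline FMA-UE, which is already collected.
3. Report hours and guideline attainment by arm, descriptively.
4. For the mediator-outcome step, do not simply drop hours. Either use a method that allows a mediator-outcome confounder affected by treatment (interventional effects, or hours as a further mediator), or report direct and indirect effects with and without hours. In the second case label them exploratory. Hours and the mediator change span the same 90 days, so the assumed time order should be stated.

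The cost is a change of wording, slightly more analysis work, and some lost precision from this covariate. No data collection or sample size changes, and the final analysis plan is still to be validated before unblinding.

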### Trial coordination and data safety monitoring

The coordinating centre for this trial is based at HUG, where the sponsor-investigator, trial management team and all operational units are located.

Day-to-day trial operations are managed by a dedicated research team, including coinvestigators and study coordinators. This team oversees patient recruitment, protocol adherence, scheduling of assessments and communication among the trial’s various operational components. The research team will meet regularly—on a weekly or biweekly basis—to ensure smooth trial progress and resolve any logistical or clinical issues.

The CTU at HUG (Geneva University Hospital) will provide monitoring services via a dedicated monitoring plan that has been approved by the ethics committee and regulatory authorities. Statistical support will be ensured by the Department of Clinical Epidemiology, and biological and imaging analyses will be conducted by specialised laboratory services at HUG. These groups will collaborate with the coordinating centre to maintain data quality and regulatory compliance throughout the trial.

A Data Safety Monitoring Board (DSMB) will be established to independently monitor participant safety and oversee safety-related aspects of the study. The DSMB will remain blind to treatment allocation and will make decisions based on expected incidence of AEs in the stroke population. Decision to suspend, terminate or amend the trial belongs to the sponsor-investigator. All AEs and SAEs will be collected, fully investigated, and documented from the time of informed consent until the completion of the last protocol-specific procedure, including the 6-month follow-up (Day 180±14). There are no planned interim analyses for efficacy. The Geneva University Hospital has contracted an insurance to compensate patients who suffer harm from trial participation.

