### Blinding and randomisation

Trial participants, care providers, outcome assessors, investigators and the study team will be blinded to treatment allocation throughout the trial. Blinding is maintained by the pharmacy of the Clinical Trial Unit (CTU), which prepares identical capsules containing either maraviroc 150 mg or placebo, indistinguishable in appearance and packaging. Each treatment bottle is labelled with a unique randomisation number. All trial data are managed through the SecuTrial clinical database, which is fully blinded to treatment assignment. Study unblinding will occur only after database lock and validation of the final statistical analysis plan by the investigators and sponsor. Unblinding of an individual participant’s allocation is only permitted in the event of a serious adverse event (SAE), when knowledge of the treatment arm is essential for clinical decision-making.

Randomisation (1:1) will be conducted by an independent statistician from the CTU at the Geneva University Hospital. A computer-generated list will be created using random permuted blocks of variable sizes (2, 4 and 6) to ensure allocation concealment. Stratification will be performed by:

Side of infarct (left vs right hemisphere)Degree of finger extension (Fugl-Meyer Extension Subscore: 1 or 2 points)

This results in four randomisation strata, ensuring balance across treatment arms with respect to the laterality and severity of motor impairment.

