### Safety outcomes

CTCAE v5.0-defined AEs through 180 days, including major adverse cardiovascular events (ie, acute myocardial infarction, acute coronary syndrome, stroke, heart failure, cardiovascular and all-cause mortality, revascularisation), liver-related AEs and infectious complications. SAEs will be tracked continuously through 180 days post randomisation.

Blood samples will be collected at each visit for safety monitoring. Participants of childbearing potential will undergo a urine pregnancy test at each visit. Samples will be processed and stored under standardised conditions.

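### Safety is defined and collected to day 180 but summarised by arm only to day 90; separately, the blinded DSMB relies on an outside event rate that may not fit this selected population

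*Protocol article*

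**What the plan says.** **Safety window.** The Safety outcomes section sets the outcome as "CTCAE v5.0-defined AEs through 180 days" and adds: "SAEs will be tracked continuously through 180 days post randomisation". The section on trial coordination and data safety monitoring has AEs and SAEs collected up to the six-month visit, day 180 with a 14-day margin. The section on statistical methods for primary and secondary outcomes then plans: "Safety analyses will summarise the number and proportion of participants with ≥1 SAE, AE of special interest, or death by day 90". That sentence ends by saying the summary is given for each group. No by-group safety summary to day 180 is stated.

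**Monitoring.** The coordination section says: "The DSMB will remain blind to treatment allocation and will make decisions based on expected incidence of AEs in the stroke population". It gives no expected rate, source or threshold. On who acts, it says: "Decision to suspend, terminate or amend the trial belongs to the sponsor-investigator". The section on blinding and randomisation says: "Trial participants, care providers, outcome assessors, investigators and the study team will be blinded to treatment allocation throughout the trial". The sponsor-investigator, as an investigator, is therefore blinded too. Box 1 excludes, among others, patients with cardiovascular comorbidities and a risk of orthostatic hypotension, significant liver or renal disease, or a prestroke modified Rankin Scale above 2.

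**The concern.** There are two separate issues.

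1. The outcome and its analysis cover different periods. If the plan is followed as written, events in the second half of the defined safety window are collected but never set out by arm. Assessing safety is a stated aim of the trial, so a defined safety outcome should have a matching summary.

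2. During the trial, nobody is stated to compare the arms. The DSMB's yardstick is "expected incidence of AEs in the stroke population", while the exclusions remove patients likely to have more cardiovascular, liver and renal events. If the yardstick is higher than the risk of the patients actually enrolled, there is room for an excess on drug before the overall count looks unusual. The concurrent placebo arm would give the right background rate, but the monitoring plan does not use it.

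**Working it through.** **Step 1: the windows side by side.**

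| Item | Period | Section |
|---|---|---|
| Treatment | 90 days | Study design |
| AE outcome | 180 days | Safety outcomes |
| SAE tracking | 180 days after randomisation | Safety outcomes |
| AE and SAE collection | to day 180 ± 14 | Trial coordination and data safety monitoring |
| By-group summary | to day 90 | Statistical methods for primary and secondary outcomes |

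Period without a stated by-arm summary: 180 − 90 = 90 days, or 90/180 = 50% of the window. Nearly all of it is after treatment ends. The boundary is approximate because visits are counted from stroke, SAE tracking is counted from randomisation, and randomisation may be up to 7 days after stroke.

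**Step 2: the plan's only computed figure.** From the sample size section: difference 12.4, SD 17.5, 5% type I error (taken as two-sided), 80% power, 20% dropout.

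n per arm = 2(1.960 + 0.842)² × 17.5²/12.4² = 2 × 7.849 × 306.25/153.76 = 31.3, rounded up to 32. Then 32/(1 − 0.20) = 40 per arm, 80 in total. This reproduces the stated 80 and gives the 40 per arm used below.

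**Step 3: how well a pooled count detects harm.** The documents give no event rates, so all risks and benchmarks here are assumptions. The drug is assumed to double the risk.

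- Pooled rule: flag if the total count X reaches the smallest r with P(X ≥ r | 80, benchmark) ≤ 0.05.
- By-arm rule: one-sided Fisher exact test at 5%, 40 v 40.
- Flag rates are exact sums over the two binomial distributions.

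| True risk, placebo / drug | Benchmark | r (of 80) | Pooled flags | By-arm Fisher flags |
|---|---|---|---|---|
| 5% / 10% | 5% | 8 | 25.0% | 8.7% |
| 5% / 10% | 7.5% | 11 | 3.6% | 8.7% |
| 10% / 20% | 10% | 14 | 30.8% | 24.5% |
| 10% / 20% | 12.5% | 16 | 13.5% | 24.5% |
| 10% / 20% | 15% | 18 | 4.6% | 24.5% |
| 20% / 40% | 20% | 23 | 64.1% | 53.8% |
| 20% / 40% | 25% | 27 | 26.3% | 53.8% |
| 20% / 40% | 30% | 32 | 3.3% | 53.8% |

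The reason is simple. When risk p doubles on drug, the pooled risk is (p + 2p)/2 = 1.5p. A benchmark of 1.5p therefore expects exactly the count that the harm produces. For 20% v 40%: 40 × 0.20 + 40 × 0.40 = 24 = 80 × 0.30.

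**Step 4: an earlier look.** With 20 per arm and 20% v 40%, pooled review flags 2.9% (30% benchmark) or 42.2% (20% benchmark), against 29.0% by arm. For 10% v 20%: 2.9% (15% benchmark) or 24.2% (10% benchmark), against 10.9%. The pattern is the same.

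**Step 5: sensitivity to the by-arm test.** Fisher's test is conservative in samples this small. A normal-approximation test with 40 per arm flags 21.2%, 34.6% and 62.3% in the three scenarios, close to the pooled rule with a correct benchmark (25.0%, 30.8% and 64.1%). So a well-set benchmark performs about as well as a by-arm comparison, and one set 1.5 times too high loses nearly all detection.

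**The case against.** A reader might infer that a drug-related excess would go unseen altogether. The documents do not support that. The day-90 summary is given for each group and covers essentially the whole treatment period, so an excess on treatment would appear at the end of the trial. What lacks a stated comparison is the later, largely off-drug period.

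A reader might also infer that blinded review necessarily hides harm. It does not: with the benchmark equal to the control risk, the pooled rule does at least as well as Fisher's test in every scenario above. Masking depends on a benchmark that is too high. Box 1 makes that plausible, but no figure in the article shows it.

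Third, pooled is not the article's word. A board blind to allocation could in principle see tables coded A and B, and table formats belong in a charter that an article would leave out. That stands as a caution. Still, the stated basis for decisions is an outside incidence and not a comparison between arms.

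There are other safeguards: blood tests at each visit, patient-level discontinuation criteria, and individual unblinding for an SAE when clinically essential. They protect individuals but do not reveal an imbalance between arms. That the final decision rests with the sponsor-investigator is not itself a fault, and AE tables by grade can be left to the analysis plan. A separate analysis plan might also add a day-180 table, but the article itself names day 90 against its own 180-day outcome.

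**Conclusion.** The window mismatch holds on the text alone and needs no assumption: half of the defined safety period has no stated by-arm summary. Its weight is moderate, since the treatment period is covered.

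The monitoring point holds as a weakness of design, not as a demonstrated error. It rests on three assumptions: that the board works from pooled counts, that its benchmark is above the trial's control risk, and the event rates chosen for illustration. Under a doubling of risk, a benchmark 1.5 times too high leaves the pooled rule flagging 3% to 5% of trials of 80, against 9% to 54% by arm with Fisher's test. With a correct benchmark the disadvantage disappears. The article gives no way to know which case applies, and only the placebo arm supplies the control rate for these patients.

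**What to change.** 1. In the statistical methods section, summarise safety by arm to day 180 as well as to day 90, and say from which date day 90 is counted. Cost: one more set of tables from data already collected.

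2. As a cheap improvement, let the DSMB receive closed by-arm safety tables, coded A/B with the codes available on request, from the independent Clinical Trial Unit statistician who made the randomisation list. Investigators, assessors and the sponsor-investigator stay blinded. Cost: charter wording, a change to the sentence on DSMB blinding, and a short table per meeting. The downside is a small risk of information leak, which the closed report limits. Sample size and efficacy analysis are unaffected.
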